### Assignment of interventions, allocation and concealment mechanisms {16}

Patients will be randomized into either an intervention group or a control group through a 1:1 ratio using a computer-generated randomization sequence via an independent investigator, who will not be involved in the trial. Allocation concealment will be maintained using sequentially numbered sealed opaque envelopes. Each envelope contains the patient’s allocation to either control or intervention group, with a unique study patient code. An independent research assistant is responsible for keeping these envelopes unopened and allocated. The baseline is defined as the time of randomization.

### Assignment of interventions: blinding {17}

Because of the design of this trial using HFNC or NIV, neither the investigators nor the patients can be blinded to the treatment allocation.

### Recruitment {15}

We will recruit participants from the emergency department, emergency intensive care unit and respiratory intensive care unit of a large, urban, tertiary-care, teaching hospital. Investigators will explain the purpose, methods, possible risks, benefits, and rights to patients who are eligible to participant in this trial. If the participant agrees to be enrolled and meets the eligibility criteria, the investigator will ask the patient or their guardian to sign the study’s informed consent form.

### Participant retention and withdrawal

Once the participants are enrolled, the research team has the responsibility to clarify the goal and obligation to the participants in order to achieve a low rate of loss to intervention. Before the start of the intervention, investigators will take time to educate and explain the duration of the intervention and possible adverse effects to all patients and their legal representatives in details. All patients will be informed that they have the right to withdraw from the study at any time during the intervention and the Data Monitoring Committee (DMC) will discuss and analyze the reasons for dropouts with data collectors, which will be documented in a standardized form. All efforts will be made to complete the follow-up and data collection and avoid missing data. Analyses will be conducted in complete cases. We will also perform sensitivity analyses by imputing the missing data to worst cases.

The data and safety monitoring committee (DSMC) will consist of four qualified members from the Peking Union Medical College Hospital, including at least one statistician and intensive care or respiratory expert independent from the site trial staff. The DSMC is independent from the trial researchers, blinded to the assignment, and will monitor the progress of the trial and safety issues and require data for analyses.

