#### Adverse event reporting and harms {22}

Adverse events reported by the participants or noticed by the clinicians or the caring nurses will be reported directly to the DSMC and recorded in the digital case report form and data management system.

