Above all, no matter the clinical parameters or prognosis, HFNC may be noninferior to NIV. HFNC shows advantages in better patient comfort and tolerance, fewer complications, improved warming and humidification of their respiratory tracts, and better sputum excretion. However, if AECOPD patients are asleep, HFNC may increase the risk of CO_2_ retention and respiratory acidosis. On the other hand, NIV may face failure because of discomfort related to the ventilation and the mask, decreased secretion clearance, and patient–ventilator interaction mismatch.

This study aims to try to take advantage of both the strengths of HFNC and NIV to improve clinical care for AECOPD patients in the ED and critical care environments. We believe that the work of this trial will help us better understand whether HFNC with sequential NIV has any advantages over NIV alone. If this ventilatory strategy proves beneficial or non-inferior, it could provide crucial clinical evidence for improving care for AECOPD patients.

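### The safety committee is blinded to assignment, and the protocol states no route by which it can compare safety between arms or learn which arm has an excess

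*Protocol article*

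**What the plan says.** Under Participant retention and withdrawal, the protocol describes the committee's role: "The DSMC is independent from the trial researchers, blinded to the assignment, and will monitor the progress of the trial and safety issues". The same sentence ends by saying that it will "and require data for analyses". The committee has four members, "including at least one statistician and intensive care or respiratory expert independent from the site trial staff".

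Three other statements bear on the blind:

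- Under Assignment of interventions: blinding {17}, "neither the investigators nor the patients can be blinded to the treatment allocation".
- Under Adverse event reporting and harms {22}, events noticed by participants, clinicians or nurses "will be reported directly to the DSMC and recorded in the digital case report form and data management system".
- Under Participant retention and withdrawal, "the Data Monitoring Committee (DMC) will discuss and analyze the reasons for dropouts with data collectors". That paragraph says DMC and the next says DSMC. I read them as one committee, because no second one is described.

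Intubation within 24 h and all-cause mortality are secondary endpoints, and PaCO2 worsening is part of the treatment-failure endpoint (Outcomes {12}).

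**The concern.** The trial replaces NIV with HFNC during waking hours in patients who enter with hypercapnic acidosis. Harm from that substitution would appear as a difference between arms in intubation, death, stopped devices or worsening PaCO2. A committee that monitors safety needs to see that difference and to know its direction, because an excess on the new strategy may call for different advice from an excess on standard care.

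The protocol states the blind as a rule; it is not simply silent on the matter. It says nothing about coded or unblinded tables, an unblinded statistician reporting to the committee, or unmasking on a safety signal. The blind also has little stated benefit. Blinding protects trial conduct and outcome assessment, but the committee is independent of the trial researchers and no section gives it outcomes to assess.

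**Working it through.** No figure in the protocol is in dispute. The check has two parts.

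**1. What each reading of the blind lets the committee see**

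Inputs: 66 patients (Abstract, Methods) allocated 1:1 (Assignment of interventions {16}), so 33 per arm. The protocol gives no expected event rate, so a total of 8 intubations is an assumption: 8/66 = 12.1% pooled.

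With the total fixed at 8, the chance of *a* events in one arm when the arms do not differ is C(33, a) × C(33, 8 − a) / C(66, 8). The two-sided Fisher p adds the probabilities of all splits that are no more likely than the one observed. For 0/8:

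2 × C(33, 8) / C(66, 8) = 2 × 13,884,156 / 5,743,572,120 = 0.0048

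| Split of 8 events (33 per arm) | Pooled report | Coded A/B report | Two-sided Fisher p |
|---|---|---|---|
| 4 / 4 | 8/66 | 4 and 4 | 1.00 |
| 2 / 6 | 8/66 | 2 and 6 | 0.26 |
| 1 / 7 | 8/66 | 1 and 7 | 0.054 |
| 0 / 8 | 8/66 | 0 and 8 | 0.005 |

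The pooled column never changes. The coded column does, but it does not say whether the arm with more events is HFNC with sequential NIV or NIV alone.

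Other assumed totals behave the same way:

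- 4 events: 2/2 gives p = 1.00 and 0/4 gives p = 0.11.
- 6 events: 3/3 gives p = 1.00 and 0/6 gives p = 0.024.
- 10 events: 5/5 gives p = 1.00 and 1/9 gives p = 0.013.

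The total decides how extreme a hidden split can be. It does not change the fact that a pooled report hides it. These p-values measure how unlike the splits are; they are not proposed as monitoring boundaries.

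**2. Whether the blind fits the protocol's own procedures**

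| Provision | Effect on the blind |
|---|---|
| Investigators and patients know the arm (blinding {17}) | Every reporter of an event knows the arm |
| Adverse events go directly to the committee (harms {22}) | No masking step is described, so a report may name the device |
| Dropout reasons are discussed with data collectors (Participant retention and withdrawal) | The data collectors work in an unblinded trial, so the talk may reveal the arm |
| Device settings and complaints such as noise, gastric distension or claustrophobia are recorded (Data collection {18}) | Case data can point to the device |

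So there are two outcomes. If the blind holds, comparison between arms is impaired. If it leaks, the committee learns the arm case by case, without orderly tables by arm. Neither serves safety review well.

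**The case against.** **The text does not say that the committee sees only pooled data.** A reader might infer that the committee cannot see an excess in one arm. The documents do not support that. Blinding to assignment is also compatible with reports by masked code, in which 4/4 and 0/8 look different, and the committee may ask for data. This objection stands, and the point is limited accordingly. The power to ask for data does not settle the matter, because the same sentence keeps the committee blinded.

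**A charter or full protocol may hold the details.** Report format and unmasking rules often sit there, and their absence from an article is not a finding. That stands for the details. It does not remove a blinding rule that the article states outright. If a charter allows unmasking, the sentence misleads and needs the same correction.

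**The named hazard is narrower than it looks.** The Discussion says that "HFNC may increase the risk of CO_2_ retention and respiratory acidosis", but only for sleeping patients, and Intervention description {11a} moves the intervention group to NIV when asleep or between 10 pm and 6 am. A reader might take the phrase as a hazard of the whole HFNC arm; the text does not say that. The point therefore does not rest on it. It rests on the waking-hours substitution, which is the experimental question.

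**Individual patients are protected.** The attending physician may stop either device (Criteria for discontinuing the trial {11b}), support is stepped up if needed (Provisions for post-trial care {30}), and monitoring is continuous with blood gases at 6, 12, 18 and 24 h (Data collection {18}). This stands, and it limits the severity. None of it gives a view between arms.

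**The event count is invented.** It is an assumption, and 0/8 is the most extreme split possible for that total. The table shows only what pooling hides; it does not predict what will happen.

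**Conclusion.** The concern holds in a limited form. The protocol makes a committee responsible for safety, blinds it to assignment, and states no route to compare arms or to identify the arm with an excess. Under pooled reporting, imbalances from 4/4 to 0/8 (p = 1.00 to 0.005 under the assumed 8 events) look identical. Under coded reporting the imbalance is visible without its direction. The blind is also hard to reconcile with direct reporting by staff who know the arm.

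The documents do not show that the committee is confined to pooled data, that a one-sided excess is likely, or that individual patients are left without safeguards. The conclusion assumes that DMC and DSMC are the same body and that no unshown document already grants access by arm. This is a cheap improvement, not a fault that undermines the trial.

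**What to change.** In Participant retention and withdrawal, replace the statement that the committee is blinded with wording such as: *The DSMC receives closed safety tables by coded arm (intubation, deaths, device stops, PaCO2 worsening), prepared by the statistician on the committee, and may unmask the codes at its own discretion. Investigators and the trial statistician do not see these tables.*

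Routine full unblinding is not needed; coded tables with a right to unmask answer the concern. If a charter already provides this, cite it in that sentence. Use one name for the committee throughout.

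The cost is one sentence and a periodic listing by a statistician who already sits on the committee. The downside is that interim data by arm will exist and must be kept confidential. No treatment rule, endpoint or sample size changes.

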### Data collection and measurement {18}

We will collect patient personal and baseline clinical characteristics as delineated above (e.g., age, gender, RASS, etc.). Furthermore, we will collect vital signs, systolic and diastolic pressure, heart rate, peripheral oxygen saturation, the presence of dyspnea based on the Borg dyspnea scale (score from 0 to 10 after 6 min’ walk, 0 means no dyspnea, 10 means the maximum), the arterial blood gas at inclusion, and starting time and settings for HFNC/NIV at 6, 12, 18, and 24 h. During the study intervention, patients will have continuous SpO_2_, electrocardiogram, respiratory rate, and noninvasive blood pressure monitoring. All relevant variables and endpoints will be evaluated at 6, 12, 18, and 24 h after randomization. In particular, we will record the NIV and HFNC settings as well as the proportion of patients who change treatment modality during the study period (i.e., switch to the other ventilatory strategy or to no ventilatory support). The discomfort score related to different ventilatory strategies will also be assessed at the established time points, and the proportion of patients showing poor tolerance to the treatment but who do not interrupt or withdrawal due to noise, temperature of flow, gastric distension, vomiting, or claustrophobia will be recorded. We will also record the rate of treatment failure due to a worsening PaCO_2_, a less than 10 mmHg reduction in PaCO_2_ from baseline, a worsening or lack of improvement in dyspnea, or a respiratory rate > 30 breaths per minute. Hospital length of stay and any-cause in-hospital mortality will all be collected. The main schedule of enrolment, intervention, and assessment were listed in the Table 1.

**Table 1 Tab1:** Schedule of enrolment, intervention, and assessment

Time point	Study period						
	Enrollment	Allocation	Post-allocation				
			Start	6 h	12 h	18 h	24 h
Enrollment							
Eligibility	** × **						
Informed consent	** × **						
Allocation		** × **					
Intervention							
Intervention group			** × **	** × **	** × **	** × **	** × **
Control group			** × **	** × **	** × **	** × **	** × **
Assessment							
Patient characteristics	** × **						
Vital signs	** × **		** × **	** × **	** × **	** × **	** × **
Medical history	** × **						
Laboratory results							
ABG			** × **	** × **	** × **	** × **	** × **
RASS score			** × **	** × **	** × **	** × **	** × **
Borg Dyspnea score			** × **				** × **
Discomfort score			** × **				** × **
Secretions							
Treatment change							** × **
Treatment failure							** × **
Endotracheal intubation							** × **

### Methods in analysis to handle protocol non-adherence and any statistical methods to handle missing data {20c}

All efforts will be made to complete the follow-up and data collection and avoid missing data. Analyses will be conducted in complete cases. We will also perform sensitivity analyses by imputing the missing data to worst cases.

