#### Outcomes {12}

The primary endpoint is the mean difference in PaCO_2_ from baseline to 24 h after randomization. Secondary endpoints include the following: (1) the mean difference in PaCO_2_ from baseline to 6, 12, and 18 h after randomization; (2) dyspnea score at 6, 12, 18, and 24 h; (3) overall discomfort score related to the ventilatory strategy and proportion of patients showing poor tolerance to treatment at 24 h (e.g., complaining about noise, pressure, temperature, gastric distension, vomiting, or claustrophobia); (4) the proportion of patients who change treatment strategies (switch to the other ventilatory strategy or to no support); (5) rate of treatment failure, defined as the proportion of patients who had PaCO_2_ worsening or reduction < 10 mmHg from baseline, or worsening with no improvement of the dyspnea or respiratory rate > 30 breaths per minute; (6) respiratory rate; (7) rate of endotracheal intubation within 24 h; (8) length of hospital stay; and (9) all-cause mortality.

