#### Sample size calculation {14}

Based on previous studies [21], we set the non-inferiority cutoff at 5 mmHg. So, we assume that in the intervention group, PaCO_2_ may not elevate more than 5 mmHg after 24 h of the high-flow nasal cannula therapy with sequential noninvasive ventilation. According to previous studies, we also assume that the PaCO_2_ of intervention group is around 54 mmHg, and the control group is around 55 mmHg. Standard deviation is 9 mmHg, after 1:1 ratio randomization, and to assess non-inferiority using an *α* = 0.05, power = 0.80, and 1-side testing, 58 subjects were needed totally. Allowing for 10% loss to follow-up, we assume that we will need to recruit 70 patients. However, if loss to follow-up is greater than 10%, we aim to continue recruitment until 58 patients have a primary outcome recorded.

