### Statistical analysis {20}

The primary and secondary endpoints will be analyzed according to the intention-to-treat principle. We will use descriptive statistical methods to measure patient characteristics and baseline clinical features. For primary and secondary outcomes, continuous variables will be presented as means ± standard deviations or median interquartile ranges (IQR). Categorical variables will be expressed as counts with percentages. We will use Student’s *T* tests or Mann–Whitney *U* tests to evaluate the differences between treatments in continuous variables according to normal distribution. Categorical variables will be compared using chi-squared or Fisher’s exact tests. All data collected will be analyzed by an independent statistical expert using SPSS (SPSS 22.0). A *p*-value < 0.05 will be considered statistically significant.

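### Intention-to-treat is promised but complete cases are the main analysis, so patients without a 24 h PaCO2 drop out of the non-inferiority comparison, and the worst-case check names no arm

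*Protocol article*

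**What the plan says.** Four statements in the protocol article bear on who is analysed.

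- Statistical analysis {20}: "The primary and secondary endpoints will be analyzed according to the intention-to-treat principle".
- Methods in analysis to handle protocol non-adherence and missing data {20c}, repeated under Participant retention and withdrawal: "Analyses will be conducted in complete cases".
- The same two sections add a check: "We will also perform sensitivity analyses by imputing the missing data to worst cases". They give neither a value nor a rule by arm.
- Sample size calculation {14}: "if loss to follow-up is greater than 10%, we aim to continue recruitment until 58 patients have a primary outcome recorded".

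The endpoint at issue is defined in Outcomes {12}: "The primary endpoint is the mean difference in PaCO_2_ from baseline to 24 h after randomization". Table 1 schedules blood gases at the start and at 6, 12, 18 and 24 h in both arms. The section on discontinuing {11b} lets the physician cease HFNC or NIV for worsening and mentions possible intubation. It does not say whether the 24 h gas is still taken and used afterwards.

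**The concern.** Intention-to-treat keeps every randomised patient in the allocated arm, whereas a complete-case analysis keeps only those with a 24 h value. The article fixes the second as the main analysis and leaves the alternative to a sensitivity analysis. This is a stated rule, so it is more than detail deferred to an analysis plan.

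Follow-up is 24 h in hospital, so ordinary loss to follow-up should be small. Values that are missing are then more likely to come from death, withdrawal or deterioration, which are related to PaCO2. If such losses differ between arms, the completers are no longer a randomised comparison, and recruiting more completers does not repair that. At stake is the error rate of the primary non-inferiority conclusion.

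**Working it through.** **Inputs from Sample size calculation {14}.** Margin 5 mmHg ("we set the non-inferiority cutoff at 5 mmHg"); means of 54 and 55 mmHg ("intervention group is around 54 mmHg, and the control group is around 55 mmHg"), so a true difference of -1; SD 9; one-sided alpha 0.05; power 0.80; 58 evaluable patients. The article gives no missing rates, so all rates below are assumptions.

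**1. Reproduce 58.** Normal approximation: n per arm = 2 × 9² × (1.645 + 0.842)² / (5 + 1)² = 27.8, so 28 per arm and 56 in total. With the exact t distribution, 28 per arm gives power 0.793 and 29 per arm gives 0.806. Hence 29 per arm, 58 in total, as stated.

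**2. When does extra recruitment start?** The Abstract enrols 66 and the sample size section 70. Fifty-eight outcomes remain until loss exceeds (66 - 58)/66 = 12.1%, or (70 - 58)/70 = 17.1%. The complete-case exclusion applies at any level of loss.

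**3. Size of the complete-case bias.** Suppose a fraction f is missing, chosen from the top of a score that has correlation ρ with 24 h PaCO2. The completers' mean then shifts by -ρ × 9 × φ(z)/(1 - f), where z is the 1 - f normal quantile. At ρ = 1:

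- f = 15%: 9 × 0.2332/0.85 = 2.47 mmHg
- f = 5%: 9 × 0.1031/0.95 = 0.98 mmHg

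With 15% missing in the intervention arm and 5% in the control arm, a true deficit of 5 mmHg is estimated as 5 - (2.47 - 0.98) = 3.51. At ρ = 0.5 the shift halves, to about 4.25.

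**4. Effect on the test.** Simulation: true deficit 5 mmHg (at the margin), SD 9, recruitment until 29 per arm are observed, one-sided 5% t bound, 20,000 runs per scenario. Ranges cover ρ = 0.5 and ρ = 1.

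| Assumed loss, intervention / control | Mean estimate (truth 5.0) | False non-inferiority |
|---|---|---|
| None | 5.0 | 5.0% |
| 10% / 10% | 5.0 | 5.0-5.1% |
| 15% / 5% | 3.5-4.2 | 9.6-18.0% |
| 20% / 10% | 3.6-4.3 | 9.2-17.9% |
| 20% / 5% | 2.8-3.9 | 12.2-28.7% |
| 5% / 15% | 5.8-6.5 | 0.9-2.5% |

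With 33 randomised per arm and nobody replaced, 15% / 5% gives 9.4-17.8% and 10% / 5% gives 7.1-10.2%. The 15% / 5% result is almost the same with and without replacement, so differential loss drives the inflation and the recruitment rule does not.

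**5. The worst-case check.** Same setting, 33 per arm, with every missing value in either arm set to one common bad value, the worst observed. At 10% / 10%, false non-inferiority is 7.1-7.4%. At 5% / 15% it is 9.8-17.7%. The bad value pulls the two arm means together, or penalises controls more. Using each arm's own worst value gives less inflation, which shows that the undefined rule matters.

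**6. Does the remedy help?** Borrowing the 18 h gas (assumed correlation 0.7 with the 24 h gas) removes about a third to a half of the bias. Poor values for missing intervention patients and observed-mean values for missing controls keep false non-inferiority below 5% in the scenarios examined.

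**The case against.** A reader might infer that patients who fail before 24 h are dropped and replaced. The document does not say so. Table 1 schedules a 24 h gas for both arms, intubation and change of strategy are counted as outcomes, and the article promises efforts to complete follow-up. An intubated or switched patient with a 24 h gas stays in the allocated arm. Exclusion is certain only for those with no 24 h value. This objection stands.

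A reader might also infer that the plan favours non-inferiority as such. That requires more poor outcomes to be missing in the intervention arm. The article gives no such rate, and its Introduction and Discussion expect intolerance of NIV, the control treatment. Heavier control loss makes the complete-case analysis conservative. This also stands.

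The recruitment rule is conditional and counts outcomes without looking at their values. Overall loss in the 15% / 5% scenario is 10%, which would not trigger it. An open sample size is therefore not shown to inflate error.

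The worst-case check does catch much of the problem when loss is heavier in the intervention arm. With 35 per arm at 15% / 5%, it cuts false non-inferiority from 18.9% to 8.4% at ρ = 1, and from 9.4% to 2.5% at ρ = 0.5. It fails where loss is equal or heavier in controls, but there the complete-case result is unbiased or conservative. This is a real mitigation, although the check remains secondary and undefined. An analysis plan that is not shown may define it by arm.

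Finally, intention-to-treat can be read as analysis by allocation among those observed. If that is meant, the article should say so, because the sentence in Statistical analysis {20} carries no such limit.

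**Conclusion.** The point holds in a limited form. Intention-to-treat and complete-case analysis are both stated and disagree for randomised patients without a 24 h PaCO2. If poor outcomes are missing more often in the intervention arm, the main analysis leans towards non-inferiority: about 9-18% false non-inferiority at 15% versus 5% loss, against a nominal 5%. Equal loss leaves the error near 5%, and heavier control loss lowers it. The worst-case check, if applied as a common bad value in both arms, errs in the other situations, at about 7-18%.

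These figures rest on assumed loss rates, on missingness concentrated in patients with high PaCO2 (ρ from 0.5 to 1), and on an SD of 9 mmHg for the analysed value. They show what could happen and do not forecast what will. The documents do not support the claim that failing patients are dropped, that the bias must favour the intervention, or that the recruitment rule is its source.

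**What to change.** 1. Reconcile Statistical analysis {20} with the two complete-case statements. The primary analysis should include all randomised patients in their allocated arm.
2. State that the 24 h gas is obtained and used also after treatment is stopped, switched or escalated, unless consent is withdrawn, and state how death before 24 h enters the analysis.
3. Estimate the 24 h difference with a repeated-measures model, or with multiple imputation, using the 6, 12 and 18 h gases already scheduled. This reduces outcome-driven bias but does not remove it, since both methods assume that the observed values explain the missingness.
4. Make the sensitivity analysis conservative for non-inferiority: poor values for missing intervention patients and observed-mean or favourable values for missing controls, or a tipping-point analysis.
5. Say in Sample size calculation {14} that recruiting on to 58 outcomes restores only the number analysed. Deleting the rule is optional.

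The cost is wording, slightly more analysis work and a possibly less favourable result. No new scheduled measurement is needed.

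### The only missing-data sensitivity analysis, worst-case imputation, has no direction by arm; read plainly, it is lenient for non-inferiority when more control than intervention patients lack a 24 h PaCO2

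*Protocol article*

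**What the plan says.** The section on non-adherence and missing data {20c} gives the main approach, "Analyses will be conducted in complete cases", and one sensitivity analysis, "We will also perform sensitivity analyses by imputing the missing data to worst cases". The section Participant retention and withdrawal repeats both sentences. Neither place defines the worst case, gives a value or mentions treatment arm, and no other missing-data sensitivity analysis is described.

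The rule serves this comparison:
- **Endpoint** (Outcomes {12}): "The primary endpoint is the mean difference in PaCO_2_ from baseline to 24 h after randomization". Higher PaCO2 is worse.
- **Margin** (Sample size calculation {14}): "we set the non-inferiority cutoff at 5 mmHg", tested one-sided at 0.05.
- **Principle** (Statistical analysis {20}): "The primary and secondary endpoints will be analyzed according to the intention-to-treat principle".
- **Expected loss** (Sample size calculation {14}): "Allowing for 10% loss to follow-up, we assume that we will need to recruit 70 patients". No split by arm is given. If loss is greater, recruitment goes on until 58 primary outcomes are recorded, so the number missing is not capped.

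**The concern.** In a superiority trial, giving every missing patient a bad value is often thought of as cautious. In a non-inferiority trial it is cautious only in the arm that has to show it is not worse. A bad PaCO2 imputed to a missing NIV patient makes the comparator look worse and narrows the apparent deficit of the HFNC strategy. If control patients are missing more often, a check meant to be pessimistic becomes easier to pass than the analysis it is meant to test.

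Control-heavy loss is plausible. The Discussion says that "NIV may face failure because of discomfort related to the ventilation and the mask", and control patients have NIV as their strategy throughout, while intervention patients have it when asleep or at night. The trial is open-label, so if the direction is left open it could also be settled after the pattern of loss is known.

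**Working it through.** **Reproducing the planned size.** Inputs from Sample size calculation {14}: margin 5, SD 9, one-sided alpha 0.05, power 0.80, and means such that the "intervention group is around 54 mmHg, and the control group is around 55 mmHg", a true difference of -1.

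n per arm = 2 × SD² × (z₀.₉₅ + z₀.₈₀)² / (margin − difference)² = 2 × 81 × (1.645 + 0.842)² / 6² ≈ 27.8, so 28 per arm. The noncentral t version gives 29 per arm, 58 in total (power 0.806), as stated.

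**Number randomised.** 58 / 0.9 = 64.4, which is 66 with equal arms, the figure in the abstract. I use 66 (33 per arm) with 58 observed, so 66 − 58 = 8 missing.

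**Shift caused by the rule.** Let W be the worst value measured from the control mean, d the true deficit, and p_I and p_C the shares missing in the intervention and control arms. With the same W in both arms, the expected estimate is

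d + p_I × (W − d) − p_C × W.

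Take d = 5 and W = 24, about the worst observed value in simulation:
- 4/4 missing: 5 + (4/33) × 19 − (4/33) × 24 = 4.4 mmHg
- 2/6 missing: 5 + (2/33) × 19 − (6/33) × 24 = 1.8 mmHg
- 0/8 missing: 5 − (8/33) × 24 = −0.8 mmHg

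Imputing an extreme value also inflates the SD, which widens the confidence limit. That is why equal loss does not make the check easier at this W, although the estimate shrinks a little.

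**One worked trial.** Observed difference +1.5, SD 9, 2/6 missing, W = 18 (2 SD, an assumption).
- Complete cases: 1.5 + 1.673 × 9 × √(1/31 + 1/27) = 5.46, which fails the 5 mmHg margin.
- Imputed: intervention mean (31 × 1.5 + 2 × 18)/33 = 2.50; control mean (6 × 18)/33 = 3.27; difference −0.77; SD 10.18. Upper limit −0.77 + 1.669 × 10.18 × √(2/33) = 3.41, which passes.
- For W from 9 to 27 the limit is 3.96 to 3.10, so the check passes throughout.
- With 8/0 missing and the same observed difference, the limit rises from 5.49 to between 6.90 and 12.41.

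**Simulated pass rates at a true deficit of 5 mmHg** (normal data, SD 9, data missing completely at random, one-sided 95% limit below 5). Complete cases pass about 5% in every row.

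| Missing, intervention/control | Same worst observed value in both arms | Worst observed value within each arm |
|---|---|---|
| 4/4 | 3.5% | 4.4% |
| 3/5 | 11% | 10% |
| 2/6 | 26% | 20% |
| 1/7 | 48% | 35% |
| 0/8 | 72% | 53% |
| 8/0 | about 0% | about 0.1% |

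A mild imputed value, no change from baseline with an assumed control change of −10 mmHg, gives 16%, 22% and 29% at 2/6, 1/7 and 0/8. The direction under control-heavy loss therefore does not depend on how the worst case is defined. With 70 randomised and 12 missing, the same-worst-value rule passes 71% at 2/10 and 3.5% at 6/6.

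**The case against.** **The text does not say that arm is ignored.** A reader might infer that the protocol prescribes one value for both arms. It does not. Worst for intervention and best for control is also a possible meaning, and under it the check passes about 0% at a true deficit of 5 mmHg in every pattern. This stands: the supportable statement is that the direction is not fixed and that the plain reading is lenient under control-heavy loss. Nor is it only detail left to an analysis plan, because the sentence commits to a rule, and following it at face value can give a misleading check.

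**Control-heavy loss is not a stated expectation.** A reader might infer from the remarks on NIV discomfort that the protocol anticipates it. Those remarks concern tolerance, not missing blood gases. Switching and poor tolerance are recorded as outcomes, a switched patient can still have a 24 h sample, and the intervention arm also uses NIV. This stands: the pattern is plausible and every split above is assumed.

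**Equal loss does not make the check easier in general.** The shrunken estimate invites that inference. With equal counts and a worst observed value the check is slightly stricter (3.5% at 4/4). Only a mild imputed value brings it a little above nominal (7.6% for no change from baseline).

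**No false trial conclusion follows.** A reader might take 26% or 72% as a false non-inferiority rate for the trial. The complete-case analysis decides, and it still passes about 5%; both analyses pass together in at most about 5%. This stands and limits the harm.

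**Missing completely at random is a simplification.** If missing patients tend to have higher PaCO2, complete cases at 2/6 are biased against HFNC, and the check passes 11–17% rather than about 26%. The size shrinks but the direction remains.

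**Conclusion.** The point holds in a limited form. The protocol's only missing-data sensitivity analysis has no direction by arm. Under its plain reading it is anti-conservative for the 5 mmHg non-inferiority comparison when more control than intervention patients lack the primary outcome: about 11%, 26% and 72% at 3/5, 2/6 and 0/8 missing, against about 5% for complete cases. With equal loss it is about neutral to slightly stricter, and with intervention-heavy loss much stricter.

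These figures rest on 66 randomised, 8 missing, SD 9, normal data, loss unrelated to outcome, and the worst observed value used in both arms. The split by arm and the imputed value are assumptions. The primary error rate does not change. What is at stake is a robustness check that can appear to support non-inferiority without adding scrutiny.

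**What to change.** In both places where the sentence appears, define the imputed value and its direction by arm, for example:

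*For the primary non-inferiority comparison, missing 24 h PaCO2 will be imputed against the intervention: the worst observed change for missing intervention patients, and the observed control mean change for missing control patients. Worst for intervention with best for control will be reported as an extreme bound.*

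Imputing the control mean should not stand alone. At a true deficit of 5 mmHg this rule passes 0.4%, 2%, 4% and 8% at 4/4, 2/6, 1/7 and 0/8, and the small excess at 0/8 arises because single imputation understates the variance. The extreme bound covers that case. A tipping-point analysis that varies the imputed values separately by arm would serve equally well.

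The cost is one sentence and no new data. The downside is a sensitivity result less favourable to non-inferiority. The extreme bound is severe: at the design difference of −1 mmHg it passes only about 4–5% at 4/4 or 2/6, against about 80% for complete cases. It should be labelled a bound, not a decision rule.
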